### Statistical analysis

All analysis will be undertaken on an intention-to-treat basis. Pain score data will be treated as non-parametric and compared using the Mann–Whitney *U* test. Multivariable predictors for higher VAS pain scores will be determined using linear/non-linear regression. Other continuous data will be compared by the Student *t* test or Mann–Whitney *U* test for parametric and non-parametric data, as appropriate. The median and first and third quartiles will be reported for continuous variables. Categorical data will be compared by the chi-square test or Fisher’s exact test, as appropriate, with a *P* value less than 0.05 indicating significance. The 5% level will be considered significant throughout. The individual undertaking the analyses will be blinded to trial allocation.

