## Methods

### Aims

The primary aim of the study is to assess patient’s pain scores for the first 10 days post procedure using a visual analogue scale (VAS). Secondary aims are to compare the two treatment groups with respect to: quality of life scores at baseline, 2 weeks and 6 months using the EQ-5D (EuroQol 5 Dimensions), AVVQ (Aberdeen Varicose Vein Questionnaire) and CIVIQ (ChronIc Venous Insufficiency quality of life Questionnaire) scores; clinical change using the VCSS (Venous Clinical Severity Score) at baseline, 2 weeks and 6 months; the degree of bruising (mild, moderate and severe) and phlebitis at 2 weeks and 6 months; patient compliance with the intervention; time taken to return to work and normal activities; patient satisfaction, assessed with a patient satisfaction questionnaire; and successful obliteration of the target vein, assessed with duplex ultrasound scan at 6 weeks and 6 months. Recanalisation will be defined by a segment of vein ≥ 5 cm. A comparison of the cost-effectiveness of the intervention will also be carried out.

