### Target population

Patients referred for treatment of symptomatic varicose veins or chronic venous insufficiency will be recruited if they are found to have primary great saphenous vein (GSV) or small saphenous vein (SSV) incompetence on colour Duplex scan.

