### Baseline

At baseline, patients will be asked to fill quality of life questionnaires (EQ-5D, AVVQ and CIVIQ; Additional files 1, 2 and 3) and will have their clinical scores assessed (CEAP and VCSS; Additional files 4 and 5). On discharge after their varicose vein intervention, the patients will then be provided with a diary to record their post-procedural pain every day for 10 days using a validated visual analogue scale (VAS) as well as to record when they return to their normal activities and are back to work (Additional files 6 and 7, respectively). They will also be asked to attend a follow-up in 2 weeks and at 6 months.

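### The effect of compression on pain is tested without covariates and the planned regression is reserved for predictors, so site, treated vein and baseline severity do not sharpen the arm comparison

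*Protocol article*

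**What the plan says.** All references are to the protocol article.

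- Statistical analysis, between-arm comparison of the primary outcome: "Pain score data will be treated as non-parametric and compared using the Mann–Whitney" U test. No covariate is named.
- Statistical analysis, next sentence: "Multivariable predictors for higher VAS pain scores will be determined using linear/non-linear regression". The terms of the model, and whether arm is one of them, are not given.
- Baseline: patients are "provided with a diary to record their post-procedural pain every day for 10 days". EQ-5D, AVVQ, CIVIQ, CEAP and VCSS are recorded before treatment. No baseline pain VAS is described.
- Study setting and Target population: there are two hospitals, one in Singapore and one in Ireland, and patients qualify with "primary great saphenous vein (GSV) or small saphenous vein (SSV) incompetence on colour Duplex scan".
- Discussion: randomisation is simple, which the authors list as a potential weakness. No stratification is described.

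**The concern.** The plan commits to a multivariable model of the primary outcome but gives it a secondary purpose. The question the trial exists to answer, whether compression changes pain, is left to a test that ignores everything known about the patient beforehand.

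Two countries, two veins and a range of baseline severity could each account for some of the spread in pain scores. With simple randomisation these factors can differ between arms by chance, and an unadjusted comparison carries that difference into the estimate. Adjustment would remove the explained part and narrow the interval. The width of the interval matters because a null result would be read as support for omitting stockings, and that reading is only as good as the differences the interval excludes.

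**Working it through.** **Inputs.** From Sample size and study duration: 94 patients, 47 per group, SD 20 mm, planned difference 20 mm, power 90%, significance 5%. From Baseline: ten daily scores per patient. Assumed, because the documents give no value: R², the share of within-arm variance in a patient's pain score explained by the covariates, 0 to about 0.4; and the within-patient correlation (ICC) of daily scores, 0.3 to 0.7.

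**1. The plan's own figure.** n per group = 2 × (1.960 + 1.282)² × 20²/20² = 2 × 10.51 = 21.01, so 22 (23 with the exact t distribution, 25–27 allowing for Mann–Whitney efficiency). The stated 47 is not reproduced. That is a separate matter; 47 per group is taken as given here. The proportional gains in step 3 do not depend on n.

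**2. Unadjusted precision.** SE = 20 × √(2/47) = 4.13 mm. The 95% half-width is 1.986 × 4.126 = 8.2 mm.

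**3. Adjusted precision.** SE(adjusted) = 4.126 × √(1 − R²). Power by normal approximation = Φ(difference/SE − 1.96).

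| R² | SE (mm) | Fall in SE | 95% half-width (mm) | Power at 10 mm | Power at 20 mm |
|---|---|---|---|---|---|
| 0 | 4.13 | none | 8.2 | 0.68 | 0.998 |
| 0.10 | 3.91 | 5% | 7.8 | 0.72 | above 0.999 |
| 0.20 | 3.69 | 11% | 7.3 | 0.77 | above 0.999 |
| 0.30 | 3.45 | 16% | 6.9 | 0.83 | above 0.999 |
| 0.40 | 3.20 | 23% | 6.3 | 0.88 | above 0.999 |

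**4. Simulation against the Mann–Whitney test.** Settings: 94 patients, simple randomisation, total SD 20 mm, normal errors, true difference 10 mm. The three scenarios assume a site effect of 10, 15 or 15 mm, a vein effect of 5, 10 or 10 mm, and a severity correlation of 0.2, 0.3 or 0.5. These give R² of 0.11, 0.27 and 0.43.

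| R² | Mann–Whitney | Linear model with covariates |
|---|---|---|
| 0 | 0.64 | 0.65 |
| 0.11 | 0.64 | 0.70 |
| 0.27 | 0.65 | 0.79 |
| 0.43 | 0.63 | 0.88 |

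Type I error in the three covariate scenarios was 0.042–0.048 for Mann–Whitney and 0.048–0.053 for the adjusted model, so both hold their size. An unadjusted t test gave 0.68 at R² = 0 and 0.67 at R² = 0.11. At low R², therefore, about half of the rise over Mann–Whitney comes from leaving the rank test under normal errors, and about half from the covariates.

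**5. Skewed scores.** With right-skewed errors at low R² and a 10 mm shift, power was 0.79 for Mann–Whitney, 0.69 for the linear adjusted model and 0.84 for a covariate-adjusted rank analysis. Adjustment still helps there, but replacing ranks by a linear model does not.

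**6. If ten daily rows were pooled as independent.** Design effect = 1 + 9 × ICC. The false-positive rate for a useless patient-level predictor is 2 × (1 − Φ(1.96/√design effect)).

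- ICC 0.3: design effect 3.7, rate 0.31.
- ICC 0.5: design effect 5.5, rate 0.40.
- ICC 0.7: design effect 7.3, rate 0.47.

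Simulation gave 0.31, 0.40 and 0.48. With one mean score per patient it gave about 0.05 throughout.

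**The case against.** **The unadjusted test is not wrong.** Under randomisation a Mann–Whitney test holds its size, and chance imbalance is sampling variation that the test already allows for. This stands. Nothing here shows bias in the primary comparison, and a reader should not infer any.

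**The gain rests on values the documents do not give.** This also stands. The simulated site effects of 10–15 mm are half to three-quarters of the planned 20 mm difference. The covariate likeliest to be strong, pain before the procedure, is not described as collected, so the lower end of the range is the more cautious expectation. At R² = 0 there is no gain and a few degrees of freedom are spent. At the planned 20 mm, power has almost no room to rise; only the interval improves.

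**Pain was deliberately treated as non-parametric.** Step 5 supports that choice if scores are skewed. It is a reason to keep the rank test and add an adjusted estimate beside it. It is not a reason to have no adjusted estimate.

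**Arm may be a term in the regression.** If so, an adjusted coefficient would be produced. But the stated purpose is to find predictors, and nothing marks that coefficient as the adjusted effect of compression or fixes its covariates.

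**A stronger reading is tempting: that the regression will produce false predictors.** With ten diary scores per patient and only ordinary regression named, a reader might infer that daily rows will be analysed as independent. The article does not say so. A per-patient mean or other summary would have nominal error, and the unit of analysis is a detail an article may leave to the full plan. Step 6 is a caution about one possible implementation; it does not describe what is planned.

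**Conclusion.** The point holds as one of efficiency. The article assigns the arm comparison to an unadjusted test and the multivariable model to predictors, so baseline information already held does not contribute to the estimated effect of compression.

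If the covariates explain 10–40% of the variance, the standard error falls by about 5–23% and the 95% half-width goes from 8.2 mm to between 7.8 and 6.3 mm. Power for a 10 mm difference rises from about 0.64 to 0.70–0.88 with normal errors. These figures rest on the assumed R², the plan's SD of 20 mm and 47 per group. Validity is not in question, and the trial is not short of power for 20 mm on its own inputs. The change is worth making because it costs almost nothing.

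**What to change.** Keep the Mann–Whitney test. In the analysis plan, give the regression a second, named purpose:

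- Fit it to one prespecified pain score per patient, with arm, site, treated vein (GSV or SSV), baseline VCSS and baseline CIVIQ as terms.
- Report the arm coefficient with a 95% confidence interval as the adjusted effect of compression. Use a linear model with robust standard errors, and state in advance that a covariate-adjusted rank-based or ordinal analysis will be given if scores are skewed.
- Label the coefficients of the other terms descriptive.
- If daily scores are modelled instead, include a patient random effect, so that patient-level terms are not tested as though there were ten independent observations per patient.

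**Cost.** A few sentences and a little analysis work, with no new data. The covariates and the per-patient score must be fixed before unblinding, and a few degrees of freedom are lost if the covariates prove not to be prognostic. The article states that recruitment had not begun, so the change can be made without reference to any data.

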### Sample size and study duration

The sample size needed to observe a difference of at least 20 mm in the VAS score with a standard deviation of 20 mm was estimated. With power of 90% and 5% significance equivalence, a minimum of 94 patients (47 per group) will need to be recruited. Accounting for losses to follow-up in the order of 10% gives a target sample size of 103 patients.

Previous studies looking at compression stockings have shown high drop-out rates close to 40% at 3 months. We do not anticipate this problem with the set up in the outpatient clinic at Changi General Hospital in Singapore. If we estimate 10% drop-out, this would mean we would need near to 200 patients to be included in this study. If three patients are recruited per week, this would take approximately 17 months to recruit the necessary number of patients. With 6 months follow-up, therefore, the study will be running for 23 months, but 3 years would give a good safety net for recruitment and follow-up, and allow for dropouts. We aim to have recruited 100 patients within the first 12 months of the study.

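### EQ-5D, AVVQ, CIVIQ and VCSS have a baseline measurement that the stated two-sample tests do not adjust for, which costs precision in these secondary comparisons

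*Protocol article*

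**What the plan says.** Among the secondary aims, the two groups are compared on "quality of life scores at baseline, 2 weeks and 6 months using the EQ-5D", AVVQ and CIVIQ, and on "clinical change using the VCSS (Venous Clinical Severity Score) at baseline, 2 weeks and 6 months" (Aims). The Baseline section confirms that the data will exist: "At baseline, patients will be asked to fill quality of life questionnaires", and VCSS is assessed at the same point. The Follow-up section repeats all four scores at 2 weeks and at 6 months.

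The Statistical analysis section gives pain its own test. For everything else on a continuous scale it says "Other continuous data will be compared by the Student" t test or the Mann–Whitney U test, depending on distribution. The only regression in the plan concerns pain: "Multivariable predictors for higher VAS pain scores will be determined using linear/non-linear regression". No baseline covariate, ANCOVA or mixed model is named for quality of life or VCSS. The section also does not say whether the two-sample tests are applied to follow-up values or to changes from baseline.

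**The concern.** Baseline scores are usually correlated with later scores on the same instrument, so part of the spread at 2 weeks and 6 months can be predicted before treatment. A two-sample test on follow-up values leaves that part in the error term. A test on changes subtracts the whole baseline value, which over-corrects unless r is 1. Neither makes the best use of a measurement that the trial has already paid for.

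Chance imbalance adds to this. The Discussion acknowledges that simple randomisation was chosen, and no stratification or other balancing is described. Baseline severity can therefore differ between the arms by chance, and both unadjusted analyses carry part of that difference into the result. The sample size was set for pain, so the article states no power for these scores.

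At stake is the precision of the secondary comparisons, and how far a single realised trial can be misled by an uneven start. The validity of the tests is not at stake.

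**Working it through.** **The plan's own figures.** The article gives no sample size, power or correlation for quality of life or VCSS. Its only calculation is for pain, to detect "a difference of at least 20 mm in the VAS score with a standard deviation of 20 mm": "With power of 90% and 5% significance equivalence, a minimum of 94 patients (47 per group) will need to be recruited". The usual two-sided formula gives 2 × (1.960 + 1.282)² × (20/20)² ≈ 21.0, so 22 per group, and 47 is not reproduced. That is a separate matter. The 47 per group is used below only to illustrate power. The percentage reductions do not depend on it.

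**Inputs.** n = 47 per group (Sample size and study duration). The baseline-to-follow-up correlation r is not in the article, so 0.3, 0.5 and 0.7 are assumed. Equal SDs at baseline and follow-up are also assumed.

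**Variance of the group difference**, relative to a test on follow-up values:

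- follow-up values only: 1
- change from baseline: 2(1 − r)
- ANCOVA on baseline: 1 − r²

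For 0 < r < 1, 1 − r² is below 1. It is also below 2(1 − r), because (1 − r²) / [2(1 − r)] = (1 + r)/2 < 1. The direction is therefore the same on either reading of the plan.

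| r | Change score | ANCOVA | ANCOVA saving vs follow-up only | ANCOVA saving vs change score |
|---|---|---|---|---|
| 0.3 | 1.40 | 0.91 | 9% | 1 − 0.91/1.40 = 35% |
| 0.5 | 1.00 | 0.75 | 25% | 1 − 0.75/1.00 = 25% |
| 0.7 | 0.60 | 0.51 | 49% | 1 − 0.51/0.60 = 15% |

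**Power at 47 per group.** Take the difference at which the follow-up-only test has 80% power: √(2/47) × (1.960 + 0.842) = 0.578 SD. Power under variance factor v is Φ(0.578 × √(47/2) / √v − 1.960).

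| r | Follow-up only | Change score | ANCOVA |
|---|---|---|---|
| 0.3 | 80% | 65.8% | 83.6% |
| 0.5 | 80% | 80.0% | 89.9% |
| 0.7 | 80% | 95.1% | 97.5% |

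**Chance imbalance.** The baseline difference between arms has standard error √(2/47) = 0.206 SD. A realised baseline difference D shifts the follow-up-only contrast by rD and the change-score contrast by −(1 − r)D. With D = 0.206 SD and r = 0.5, each is shifted by about 0.10 SD, in opposite directions. ANCOVA removes this linear effect.

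**Cost of adjustment.** Estimating one slope inflates the variance by about 1 + 1/(94 − 4) = 1.011, or roughly 1%. Against a follow-up-only test the gain is cancelled only when r is as low as about √(1/90) = 0.105.

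**The case against.** The strongest reply is that this is an optional efficiency gain in secondary outcomes. The t and Mann–Whitney tests keep their type I error under randomisation, and the unadjusted difference is unbiased over repeated randomisations. The primary outcome is daily pain over 10 days, for which no baseline VAS is described. No stated power claim fails, because none is made for these scores. All of this stands and limits the weight of the point.

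It can also be said that covariate adjustment is normally settled in a statistical analysis plan that is not shown here. That carries less weight, because the article does name the tests for these data, and a plan that followed it would leave baseline out as a covariate.

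Some stronger readings are tempting, but the text does not support them:

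- A reader might infer that follow-up values alone will be tested at each visit, so that baseline is ignored altogether. The article does not say so, and its wording for VCSS, "clinical change using the VCSS (Venous Clinical Severity Score) at baseline, 2 weeks and 6 months", points towards change scores. The largest saving, 49%, therefore holds only on one reading and at the top of an assumed range. At the same r the saving against change scores is 15%.
- A reader might infer that a significance test between the arms at baseline is planned. The Aims can be read that way, but the phrase equally lists the measurement schedule, and the Statistical analysis section names no such test.
- A reader might add site as a covariate. Nothing in this point argues for that, and the article describes no stratification by site.

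Finally, the 1 − r² formula concerns differences in means. It does not carry over directly where the Mann–Whitney test would be used.

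**Conclusion.** The point holds as a matter of precision. Whether the planned tests use follow-up values or changes, adjusting each score for its own baseline gives a smaller variance for any r between 0 and 1, apart from a loss of about 1% for the extra parameter. It also removes the linear effect of chance baseline imbalance. Across assumed r of 0.3 to 0.7, the saving runs from 9% to 49% against a follow-up-only test and from 35% down to 15% against a change-score test. These sizes rest on the assumed r, on equal SDs at the two times and on a comparison of means. The direction against a follow-up-only test does not need the equal-SD assumption. The consequence is confined to the secondary quality-of-life and VCSS comparisons.

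**What to change.** In Statistical analysis, state that EQ-5D, AVVQ, CIVIQ and VCSS will each be compared between groups at 2 weeks and at 6 months by ANCOVA (linear regression) with the score's own baseline value as covariate. Report the adjusted between-group difference with its 95% confidence interval. Name a rank-based version as a sensitivity analysis if the data are skewed.

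In Aims, reword the secondary aims so that baseline is a time of measurement and the group comparisons are those at 2 weeks and 6 months.

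The cost is a short change to the text, about one degree of freedom per model, and the need for a baseline value from each patient analysed. No new data are required. The article states that recruitment had not begun, so at that stage the change could be made before any outcome was seen.

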**Methods:**

Ethical approval for the study was obtained from the Singhealth Centralised Institutional Review Board (CIRB Ref: 2017/2710). Consent to enter the study will be sought from each participant only after a full explanation has been given, an information leaflet offered and time allowed for consideration. Signed participant consent will be obtained. Patients will be randomised to either compression (group A) or no compression (group B). The primary aim of the study is to assess the patient’s pain scores for the first 10 days post procedure using a visual analogue scale. Secondary aims include an assessment of patient compliance with compression, quality of life scores, clinical effectiveness, rates of bruising and phlebitis, time taken to return to normal activities, patient satisfaction and occlusion rate at 6 months.

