## Background

Varicose veins are common and are known to affect approximately one-third of the population [1]. Chronic venous disease (CVD) has been shown to have a negative impact on the quality of life of patients and treatment of varicose veins has been demonstrated to lead to improvement in quality of life [2–4]. Over the past decade, new endovenous techniques have been introduced and these are felt to be cost-effective, especially when performed in an outpatient or ‘office-based’ setting [5]. There is currently uncertainty about the use of compression stockings following treatment of varicose veins. In their consensus statement in 2008, the International Union of Phlebology (IUP) stated that there is good evidence for using compression in certain clinical indications [6]. These include the management of telangiectasia after sclerotherapy, varicose veins in pregnancy, prevention of thromboembolism and healing of ulcers. However, a few questions remain unanswered, such as the length of treatment and level of compression to be used [6]. The Society for Vascular Surgery and the American Venous Forum recommend using compression stockings post-operatively for 1 week to prevent haematoma formation, pain and swelling [7]. The 2013 NICE Guidelines on Varicose Veins in the Legs recommended that compression hosiery is used for no more than 7 days after interventional treatment for varicose veins [8]. However, due to current uncertainty of compression bandaging or hosiery compared to no compression after interventional treatment for varicose veins, the NICE Guideline Development Group has advocated further research to evaluate the clinical and cost effectiveness of this post-procedure intervention [8]. The guidelines also suggested looking into the length of time compression bandaging should be worn if it is shown to be beneficial [8].

Several researchers have looked into the practice of using compression after venous ablation. In a survey of the management of varicose veins by the members of the Vascular Society of Great Britain and Ireland, Edwards et al. [9] found that the majority of surgeons used bandages post-operatively, with 49% using elastic bandages. The literature on the use of compression stockings following treatment of varicose vein is limited.

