### Follow-up

Patients will be followed up in the outpatient clinic at 2 weeks and 6 months. At the 2 weeks’ follow-up, the diary containing details of the pain scores and how soon patients were able to return to normal activities/work will be collected. In addition, patients will be asked about any bruising or phlebitis they have had in the 2 weeks after their procedure and how compliant they have been with the compression. The degree of bruising and phlebitis will be assessed using a pre-determined score (0, 0%; 1, < 25% of treated vein affected; 2, 25–50% of treated vein affected; 3, 50–75% of treated vein affected; 4, 75–100% of treated vein affected; and 5, extending beyond the treated vein). They will be examined and the Venous Clinical Severity Score (VCSS) will be recorded. They will also be asked to fill in the EQ-5D, AVVQ and CIVIQ scores. They will have a venous Duplex scan to determine occlusion of the treated vein. Recanalisation will be defined by a segment ≥ 5 cm.

At the 6-month follow-up, patients will be examined and their VCSS will be recorded. They will also be asked to fill in the EQ-5D, AVVQ and the CIVIQ scores. They will have a venous Duplex scan to determine occlusion of the treated vein. An overall satisfaction survey will also be asked. A flowchart for the trial is provided in Fig. 1. The study timeline is also detailed in the SPIRIT (Standard Protocol Items: Recommendations for Interval Trials) schedule of enrolment, interventions and assessments in Fig. 2. The SPIRIT checklist is included in Additional file 8.

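### Bruising and phlebitis are recorded as ordered grades, but the analysis rule that most naturally covers them ignores the order

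*Protocol article*

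**What the plan says.** Two sections of the protocol article describe the bruising measure differently. The Aims list "the degree of bruising (mild, moderate and severe) and phlebitis at 2 weeks and 6 months", which is three grades for bruising. The Follow-up section says "The degree of bruising and phlebitis will be assessed using a pre-determined score (0, 0%; 1, < 25% of treated vein affected" and continues to grade 5, so it has six grades. Grades 1 to 4 rise with the share of the treated vein that is affected, and grade 5 is for spread past that vein.

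The abstract places both outcomes among the secondary aims: "Secondary aims include an assessment of patient compliance with compression, quality of life scores, clinical effectiveness, rates of bruising and phlebitis".

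Apart from pain, which goes to Mann-Whitney, the Statistical analysis section has two routes for comparing the arms. One is "Other continuous data will be compared by the Student *t* test or Mann–Whitney *U* test for parametric and non-parametric data, as appropriate". The other is "Categorical data will be compared by the chi-square test or Fisher’s exact test, as appropriate". Neither mentions bruising or phlebitis by name, and no trend, rank or proportional-odds method is named for graded categories. On significance it adds "The 5% level will be considered significant throughout".

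**The concern.** Mild/moderate/severe is categorical data on any plain reading, and the abstract's talk of rates points the same way. The phrase about appropriateness in that rule chooses only between chi-square and Fisher; it does not bring in an ordinal test. Both tests treat grades as unordered labels. On a 2 x 6 table chi-square spreads its sensitivity over (2-1) x (6-1) = 5 degrees of freedom, and the test itself gives neither a direction nor a size of effect.

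This matters because the trial asks whether stockings can be left out. The Background cites guidance to "recommend using compression stockings post-operatively for 1 week to prevent haematoma formation, pain and swelling", so a shift to worse local grades without stockings is a result that readers will look for. A test that ignores order may miss a consistent shift that the same data would show under an ordinal analysis.

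**Working it through.** **Inputs from the article.** 47 per group and a 5% level. Two-sided testing is assumed, because sidedness is not stated. The grade scales are 0-5 (Follow-up) and three grades (Aims).

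**The plan's own figure.** The article gives no power figure for bruising or phlebitis. The only powered outcome is pain: "a difference of at least 20 mm in the VAS score with a standard deviation of 20 mm", 90% power. The usual formula gives 2 x (1.960 + 1.282)² x (20/20)² = 21.0, so 22 per group, not 47. That mismatch is a separate matter, as is the conflict between 103 and nearly 200 patients in the same section. Here 47 per arm is used only because it is the stated minimum.

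**Inputs that are assumptions.** The grade distribution and the effect size.

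**Method.** The arms differ by a common odds ratio (OR): odds(grade ≤ k) in one arm = OR x odds(grade ≤ k) in the other, for every k. For example, take .35/.25/.18/.12/.07/.03 over grades 0-5 in the worse arm and OR 2. At the first cut the odds are .35/.65 = 0.538, doubled to 1.077, so grade 0 has probability 1.077/2.077 = .52 in the milder arm. At the second cut the odds are .60/.40 = 1.5, doubled to 3, so grades 0-1 have probability .75.

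Each simulated table is tested in two ways:
- Pearson chi-square: the sum of (O - E)²/E, with empty grades dropped.
- Tie-corrected Mann-Whitney: z = (W - n(N+1)/2)/√v, with v = (n²/12) x [(N+1) - Σ(t³ - t)/(N(N-1))]. Here n = 47, N = 94, W is one arm's sum of mid-ranks, and t is the total in each grade.

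**Result for that spread, 47 per arm** (20,000 runs per OR):

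| OR | Chi-square | Mann-Whitney | Gap (points) |
|---|---|---|---|
| 1.5 | 9.5% | 19.0% | 9.5 |
| 2 | 22.0% | 44.2% | 22.2 |
| 2.5 | 38.4% | 66.9% | 28.5 |
| 3 | 53.6% | 80.4% | 26.8 |
| 4 | 76.0% | 93.8% | 17.8 |

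**Other settings under a uniform shift:**
- Five assumed six-grade spreads, 47 per arm: the gap is 7 to 32 points. For most spreads it peaks around OR 2 to 3. When most patients have grade 0 (.80/.10/.05/.03/.01/.01) it is still rising at OR 4; at 51 per arm it is 26.5% against 58.9% there.
- Fisher's exact test, 47 per arm (2,000 runs): for the spread in the table the gaps at OR 1.5 to 4 are about 7, 20, 23, 23 and 12 points. Over the spreads tried, the range is about 3 to 23.
- Three grades, chi-square: about 3 to 14 points. With .5/.3/.2 it is about 4 to 11.
- Six grades at 90 to 100 per arm: from below 1 to 31 points.
- With no true difference and six grades at 51 per arm, Mann-Whitney rejects in 4.8% to 5.1% of runs and chi-square in 2.4% to 4.7%. The gain does not come from an inflated error rate.

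**When the effect is not a uniform shift** (47 per arm): for an effect confined to the most severe grades, chi-square has 34% power and Mann-Whitney 6%. For a difference in spread it is 95.5% against 6.7%.

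**The case against.** The strongest reply is that the article assigns these outcomes to no test. The Follow-up section calls the 0-5 measure a score. Pain scores go to Mann-Whitney, and other numeric scores, such as the VCSS, have no natural home except the t test/Mann-Whitney route. A 0-5 score can be read the same way, and the plan would then already use an adequate test. This stands in part: that the grades go to chi-square or Fisher is an inference, not a stated fact. It does not settle the point. Under the three-grade scale in the Aims, bruising would get a test blind to order, and under the six-grade scale it might get a rank test, with no rule for choosing.

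A second reply is that a test for each secondary outcome belongs in an analysis plan that is not shown. That would answer a complaint about missing detail. Here the article does state a rule for categorical data, and the rule suits ordered grades badly. The reply does stand against any claim that no effect estimate or confidence interval will be reported; the article does not exclude them.

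A third reply is that the power gap depends on the assumptions and can reverse. That is correct, and it is why the size is given as a range.

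**Conclusion.** The point holds as a correctable weakness in the analysis of secondary outcomes. The grades are ordered, the named categorical tests ignore the order, and under a uniform shift the loss of power is material for most six-grade settings tried at 47 per arm: 7 to 32 points for chi-square and about 3 to 23 for Fisher. With three grades it is smaller, about 3 to 14 points for chi-square.

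A reader might infer more than this, in three ways that the documents do not support:
- That the plan forfeits a fixed 23 to 29 points of power. Gaps of that order arise with six grades, the Pearson test, about 47 to 51 per arm and an OR of about 2 to 3. No effect size or grade distribution is stated, and the sample size is itself unsettled.
- That these are the trial's main harm measures. The article lists them only as secondary aims.
- That an ordinal test is always better. It is much weaker when the effect sits only in the worst grades.

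**What to change.** In Statistical analysis, state that the bruising and phlebitis grades are each compared by a method that uses their order. Either of these would do: a tie-corrected Mann-Whitney test with the probability of superiority and its 95% CI, or proportional-odds regression with a common odds ratio and its 95% CI. Tabulate every grade by arm. Keep chi-square and Fisher for binary or unordered outcomes.

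Reconcile the Aims and Follow-up sections to a single bruising scale, and confirm that grade 5 ranks as worst, so that the scale is strictly ordered.

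The cost is a few sentences, with no added data, visits or patients. The downside is lower sensitivity to effects that are not a uniform shift, such as one confined to the most severe grades. The full table by arm is there to show such a pattern.
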